# 9.3. Interim analysis

The study plans to perform two interim efficacy analyses after collecting 1/2 and 2/3 primary endpoints to assess whether a valid conclusion has been reached and then terminate the study early. According to Lan-DeMets α spending function and the O'Brien-Fleming method, the spending type I error was α = 0.0001 (one side) in the first interim analysis period, and α = 0.00605 (one side) in the second interim analysis period.

The specific requirements and operations related to the interim analysis will be specified in the DSMB in advance.

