# 2. Study design

# 2.1. Rationale for study design

This study is a randomized, double-blind, placebo-controlled, parallel-group, multicenter clinical study.

The study will be event-driven, and all randomized patients will remain in the study (whether taking the study drug or not) until the number of primary endpoint events reaches the predicted value (620 cases), or the study terminates early when it meets the pre-defined efficacy or safety criteria of early termination.

Two mid-term efficacy analyses planned to be conducted after 1/2 and 2/3 primary endpoint events to assess whether an invalid or valid conclusion was reached so as to prematurely end the study.

The entire study will last approximately 36 months, and the recruitment period will be expected to be 24 months. The follow-up period after the last case of patient is included in the study is 12 months. The average follow-up time is predicted to be about 24 months.

Patients who show stable clinical symptoms, had received at least 2 weeks of standardized treatment and treatment of other concomitant diseases before enrollment are screened at the hospital. According to the local HF treatment guidelines, the drug type and dosage are fixed, unless it is contraindicated or intolerant. The patient who have not receive anti-HF drug intravenously for at least two weeks prior to enrollment, nor take oral administration of TCM or Chinese patent medicine having similar composition with Qiliqiangxin Capsule can directly enter the random grouping stage.

If patients fail to meet the above requirements, term standardized treatment to meet the above criteria before entering the random grouping stage are needed.

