# 2.2. Control group and Sample size

According to the PARADIGM-HF study, cardiovascular death or hospitalization rate for heart failure in the median follow-up of 27 months was 21.8% in the LCZ696 group and 26.5% in the Enalapril group. Therefore, we estimate that the incidence of cardiovascular death and hospitalization for heart failure is 25% in all patients of basic treatment +placebo group within 36 months of follow-up and 20% in basic treatment + Qiliqiangxin Capsule group.

The random distribution ratio is 1:1 between study group and control group. Considering the consumption of type I error in the interim analysis, α is adjusted to unilateral 0.02314. The sample size is the number of cases with composite endpoint events. It is expected that 620 composite endpoint events need be observed to provide 80% power of test (β= 0.2), and 20% risk can be reduced in study group by log-rank test.

The entire study will last approximately 36 months to follow up, and the recruitment period are expected to be 24 months. It is expected that 3,080 patients in over 100 centers (1540 patients per group, 1:1 into study group and control group) will be enrolled and be followed up at least for 12 months. Estimating the incidence of composite endpoint events is 25%, in total 620 end-point events are expected to be obtained in the analysis.

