# 9.2. Statistics methods

Efficacy analysis is taken on the basis of FAS and PPS. All baseline demographic data analysis will be performed on the basis of FAS and safety evaluation on SAS.

- All data are performed with two-sided test, and P value less than or equal to 0.05 (two-sided test) is considered with statistical difference (unless otherwise specified).
- Descriptive analysis: Classification data is described with number of cases and percentage. Quantitative data is described with mean, standard deviation, maximum value and minimum value, median, the first quartile (Q1) and third quartile (Q3).
- Comparison of general situation should be analyzed with appropriate method based on the type of index. Quantitative data should be analyzed with paired t test or Wilcoxon rank sum test; classification data with chi-square test or precise probability method, and grade data with Wilcoxon rank-sum test or CMH test.

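### The first-look alpha of 0.0001 is the O'Brien-Fleming-type spend for 1/3 of events, but the first interim look is planned at 1/2, where the named function spends 0.00153

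*Protocol*

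**What the plan says.** The timing of the looks appears twice and agrees. Section 2.1: "Two mid-term efficacy analyses planned to be conducted after 1/2 and 2/3 primary endpoint events". Section 9.3: "two interim efficacy analyses after collecting 1/2 and 2/3 primary endpoints". With 620 target events, these are looks at 310 and about 413 events.

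Section 9.3 names the method, "According to Lan-DeMets α spending function and the O'Brien-Fleming method", and gives the figures: "the spending type I error was α = 0.0001 (one side) in the first interim analysis period, and α = 0.00605 (one side" for the second look.

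Section 2.2 sets the level used for sizing: "Considering the consumption of type I error in the interim analysis, α is adjusted to unilateral 0.02314". Section 9.2 has a general rule, "P value less than or equal to 0.05 (two-sided test) is considered with statistical difference", and that sentence closes with an exemption for anything specified otherwise. Section 9.2.3 states a one-sided hypothesis, a log-rank test and a 95% confidence interval, and does not repeat a test level.

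**The concern.** A spending function fixes the alpha available at each look once the information fraction is known. The protocol gives the function, the fractions and the alphas, so the three can be checked against one another. At the first look they disagree.

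What is at stake is the efficacy stopping rule at 310 events. Anyone preparing the interim analysis can follow the printed 0.0001 or compute the boundary from the named function at 1/2, and the two boundaries are far apart. If this is noticed only when unblinded data are on the table, either choice can look data-driven.

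**Working it through.** **Inputs.** Looks at 1/2 and 2/3 of events (sections 2.1 and 9.3); Lan-DeMets with O'Brien-Fleming and one-sided alphas 0.0001 and 0.00605 (9.3); final one-sided level 0.02314, 620 events, 1:1 allocation and a 20% risk reduction, read as a hazard ratio (HR) of 0.80 (2.2). The protocol does not state the one-sided total. I take 0.025, half of the two-sided 0.05 in section 9.2.

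**Step 1: spend.** The O'Brien-Fleming-type function is α(t) = 2[1 − Φ(z/√t)], with z = Φ⁻¹(1 − 0.025/2) = 2.2414.

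| Fraction t | z/√t | Cumulative one-sided spend | Protocol figure |
|---|---|---|---|
| 1/3 | 3.882 | 0.000104 | 0.0001 (assigned to 1/2) |
| 1/2 | 3.170 | 0.001525 | – |
| 2/3 | 2.745 | 0.006048 | 0.00605 (assigned to 2/3) |

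The function reproduces 0.00605 at its stated look. It reproduces 0.0001 only at 1/3. At 1/2 the ratio is 0.001525/0.0001, about 15. A one-sided total of 0.05 does not rescue the figure: it gives 0.00069 at 1/3, 0.00557 at 1/2 and 0.01637 at 2/3.

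**Step 2: nominal levels.** Recursive integration of the joint normal distribution gives:

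- Looks at 1/2, 2/3, 1: z = 2.963, 2.538, 1.994; nominal one-sided p = 0.00153, 0.00557, 0.02305.
- Looks at 1/3, 2/3, 1: z = 3.710, 2.511, 1.993; nominal one-sided p = 0.00010, 0.00601, 0.02313.

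**Step 3: the first look at 310 events.** The boundary on the HR scale is exp(−2z/√310).

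- As written: z = 3.719, so exp(−2 × 3.719/17.607) = 0.655.
- Named function: z = 2.963, so exp(−2 × 2.963/17.607) = 0.714.

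Under HR 0.80 the expected z is 0.2231 × 17.607/2 = 1.964. The chance of crossing is 1 − Φ(3.719 − 1.964) = 4.0% as written and 1 − Φ(2.963 − 1.964) = 15.9% for the function.

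**Step 4: the whole design (620 events).** The stated levels are applied as nominal levels at 1/2, 2/3 and 1, against those of the named function.

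| | As written | Named function |
|---|---|---|
| Overall one-sided type I error | 0.0250 | 0.0250 |
| Stopped at the first look, HR 0.80 | 4.0% | 15.9% |
| Stopped by the second look, HR 0.80 | 40.5% | 40.0% |
| Overall power, HR 0.80 | 78.8% | 78.8% |

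**Step 5: the final level.** If the final primary test were run at one-sided 0.025 (two-sided 0.05) after these looks, overall one-sided error would be about 0.0268, whichever set of interim boundaries is used.

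**The case against.** The best defence is that little is lost. The printed levels, used at the planned looks, keep the overall error at 0.0250. Solving for boundaries at 1/2, 2/3 and 1 with cumulative spends of 0.0001, 0.00605 and 0.025 returns nominal levels of 0.00010, 0.00605 and 0.02314, so the figures form a valid design in their own right. Power is the same, and so, nearly, is the chance of having stopped by the second look. The cost is a stop delayed by about 103 events (413 − 310) in roughly 12% of trials (15.9% − 4.0%) if HR 0.80 is true. Section 9.3 also defers the operating details to a document for the monitoring board, which is not shown and may contain exact boundaries. All of this stands and limits the size of the point. It does not remove the contradiction, because such a document would still have to depart from the protocol's figure, its timing or its named function.

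Four stronger readings are tempting and are not supported:

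- **That the interim error inflates type I error.** It does not; it makes the first look too strict.
- **That both interim figures are wrong.** 0.00605 is the right cumulative spend at 2/3. Section 9.3 describes it as spending and does not call it a nominal p-value.
- **That the figures are shown to come from equally spaced looks.** 0.0001 matches 1/3, and 0.02314 is close to the 0.02313 of that design. But 0.02314 also follows from the printed spends at the planned looks, so the origin is only an inference.
- **That section 9.2 ignores the alpha spent.** Its 0.05 rule yields to anything specified otherwise, and section 2.2 does specify a level: "α is adjusted to unilateral 0.02314". What remains is a missing cross-reference in section 9.2.3.

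**Conclusion.** The point holds for one figure. The one-sided 0.0001 assigned to the look at 1/2 of events is not what the named function gives there; the value is 0.00153, about 15 times larger. The direction is conservative, with no effect on overall error, power or sample size. The practical consequence is confined to the first look, where an observed HR between 0.655 and 0.714 means continue under the printed figure and stop under the printed method.

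This rests on a one-sided total of 0.025, which the match at 2/3 supports. The stopping probabilities also rest on HR 0.80, 620 events and the usual normal approximation to the log-rank statistic. The unlinked final level is a minor matter of clarity: 0.0268 would arise only if the general 0.05 rule were applied to the primary test and section 2.2 were disregarded.

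**What to change.** Before the first look, make timing and figure agree in section 9.3 (and section 2.1 if the timing changes), in one of two ways:

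- Keep the looks at 1/2 and 2/3 (310 and about 413 events) and state cumulative one-sided spends of 0.00153, 0.00605 and 0.025, with nominal one-sided levels of 0.00153, 0.00557 and 0.02305.
- Move the first look to 1/3 (620/3, about 207 events) and keep 0.0001, with a final level of about 0.0231.

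In either case, give the one-sided total, label each number as cumulative spend or nominal level, and say that boundaries are recomputed at the event fraction actually reached. In section 9.2.3, refer to the adjusted final level of section 2.2 (one-sided, about 0.0231) as the level for the primary test.

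The cost is a wording change in the protocol and in the monitoring board's document. Sample size is unaffected: the final level is 0.02305 or 0.02313, against the 0.02314 used for sizing.

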# 10. Data Management

This study used Epidata software to collect research data. Data management ensures the authenticity, integrality and accuracy of clinical data. The data management process needs to comply with the regulatory requirements of Clinical Trial Quality Management Regulations and Clinical Trial Data Management Work Technical Guidelines, in order to ensure traceability of study data. The main processes for data management are listed below.

# 10.1. Database Design

The data administrator adopts the Epidata software to design and release database according to the CRF after testing.

# 10.2. Data entry

Clinical research coordinator (CRC) is responsible for inputting the CRF data into the database. The data entry adopts secondary recording mode. Two CRC respectively input the data. Data administrator compares the two databases to generate the data inconsistency list. CRC modified the databases respectively according to the list and the CRF, and then made comparison again. The above steps are repeated until the two databases being identical.

# 10.3. Data questioning management

The data administrator wrote data verification SAS program according to the data verification plan (DVP) to verify and generated a data questioning list. The data questioning table would be generated after manual verification, and clinical research auditor (CRA) gives the data questioning table to the researcher for answer. After the researcher answering the question, CRA returned the data questioning table to data administrator and revised the database accordingly.

# 10.4. Medical coding

The medical coding of adverse events is done according to MedDRA 21.0 or advance version.

# 10.5. Data audit

After completion of database cleanup, the data administrator should write Data Verification Report for holding a data verification meeting.

The major recording contents of the audit report: number of enrolled cases, the condition of off cases and exclusion cases, the condition of deviation or violation from the program, compliance data, drug combination, adverse events, data related to the evaluation indicators, etc.

At the data audit meeting, the division of statistical population is discussed and determined according to the content of audit report.

# 10.6. Database locking

Complete detailed list of database locking and complete the database locking according to the program of database locking. Problems discovered after data locking can be corrected in the statistical analysis program after confirmation. After data locking, if there is clear evidence that it is necessary to unlock, the researcher and related personnel need to sign the unlocking document. After database locking, the data file is exported by the data administrator and sent to the statistician for statistical analysis.

# 11. Quality Control

1. Main research units and researchers should perform respective duties, strictly abide by clinical research programme, adopt standard operating procedure, verify all the related observed result, find to guarantee the quality control of clinical research, and the implementation of quality assurance system.
2. The subjects in clinical research should be distributed according to random allocation program decided by research design and the block encoding of every subject should be saved by main research units and researcher as blind codes.
3. Researcher should make necessary training, explaining related information, operation standard and responsibility to all the people participating clinical research as well as guarantee to record data into case history and CRF with sincerity, accuracy, integrity, timeliness and legitimacy. CRF must be saved by specially assigned person. Participant should own the qualification certificate of project training.
4. The supervisors should take reference to standard operation procedure, supervise and urge the execution situation of research programme, affirm correctness and integrity of all data records and reports. All CRF should be filled in correctly and keep consistency with original material.
5. The sponsors entrust auditors with systematic examination on relevant clinical activity and documents to evaluate whether the study is conducted in accordance with protocol, standard operating procedure and relevant regulatory requirement or not.
6. Various laboratory inspection data in clinical research should be recorded accurately or pasted the original report copy on CRF.
7. Medical statistician should bring research data into report timely, entirely and inerrably, all steps involved in data management should be recorded to make inspection on data quality and research implementation.
8. Statistical analysis process and the expression of results of clinical research material should adopt standard statistics method. Medical statistician should participate in every phase of clinical research. Statistical report of clinical research should conform to final report of clinical research.
9. All parties should follow with approved trial program, any situation deviating from the program should be recorded. The modification of research program should formulate modification description and be carried out after submitting to Ethics Committee for approval.
10. Each study center should consist of a study principal and several permanent researchers. The study should be conducted in strict accordance with clinical study program. The technical staff in head unit should maintain close contact with the research centers at any time, and visit each study center at early, middle and late stages of the study to inspection and timely resolve any possible problem.

# 12. Ethical conduct of the study

1. The rights, interests and safety of subjects should be considered prior to any science and social interest. The personal interests of subjects should be given sufficient protection and through the entire process.
2. Research program can only be implemented after deliberation agreement and signature of approval opinion by Ethics Committee. Any modification to research program should be approved by Ethics Committee during the period of research; timely report should be submitted to Ethics Committee if serious adverse event was occurred in research.
3. Researcher or the appointed representative should state the detailed research situation to all subjects. Informed consent should be acquired after sufficient and detailed explanation to research situation.

# 13. Study timetable and end of study

| July 2018 | Complete development of study programme, and hold preparatory meeting |
| --- | --- |
| September 2018 | Modify plan and pass ethical audit |
| October 2018 | Study drug and data preparation |
| January 2019 | International registry of the study and start-up of sub-centers |
| March 2019 | Select and enroll the first case |
| October 2020 | Complete randomized grouping of all cases |
| October 2021 | Complete follow-up of all cases in each center |
| December 2021 | Complete data entry and blind review |
| April 2022 | Statistical analysis |
| June 2022 | Complete the study summary report |

# 14. Data Archiving

All study hospitals should keep these original data at least for five years after the termination of clinical study, including confirmation of all participants (effectively verify all records, such as CRF and hospital original record), informed consent, CRF form, and detailed records of drug distribution of all subjects.

# 15. Clinical Summary

After the end of statistical analysis, the main researchers are responsible for composing the clinical summary report and affixing the official seal of main research unit.

# Appendix 1: New York Heart Association (NYHA) Functional Classification

| **NYHA Class** | **Symptoms** |
| --- | --- |
| I | No limitation of physical activity. Ordinary physical activity does not cause undue fatigue, palpitation, dyspnea (shortness of breath). |
| II | Slight limitation of physical activity. Comfortable at rest. Ordinary physical activity results in fatigue, palpitation, dyspnea (shortness of breath). |
| III | Marked limitation of physical activity. Comfortable at rest. Less than ordinary activity causes fatigue, palpitation, or dyspnea. |
| IV | Unable to carry on any physical activity without discomfort. Symptoms of heart failure at rest. If any physical activity is undertaken, discomfort increases. |

# Appendix 2: NT-proBNP test, blood collection, blood sample preservation and transportation process

**Blood sample preparation test and standard operating procedures of cold chain transport**

**1． Purpose**

Standardize the preservation, transportation and reception conditions and processes of blood samples

**2．Scope of application**

Blood sample preparation, test and transportation in a randomized, double-blind, placebo-controlled multi-center clinical trial to evaluate the efficacy and safety of Qiliqiangxin Capsules in the treatment of chronic heart failure;

**3．Simple process**

Blood sample preparation

Storage Responsible party (researcher)

Handover

Transportation Responsible party (express company)

Receive

Laboratory

**4．Preparation and storage**

The blood sample should be finished preparation within 2 hours after collection according to the standard operating procedures and storage of blood samples. The blood samples should be placed in the freezer tubes respectively. Attach two sheets of the adhesive sticker to the freezer tube according to the number of the drug and the other sheet to the log sheet of reserved sample (Table 1) and fill in the log sheet of reserved sample as required.

**NT-proBNP** **sample preparation process**

Draw 3ml venous blood from each subject

EDTA anticoagulation

Centrifuge to obtain the supernatants

Label the blood samples of each patient

Storage in the refrigerator at -20℃

All samples should be sent for test within 3 months after collection

Note:

1. It should be detected in the condition of no inflammation nor infection (metabolic stability) to reduce individual differences;
2. Patient preparation: Fasting for more than 12 hours, collecting venous blood in the sitting position at 8:00 am to 9:00 am.
3. Blood collection requirements: Use a vacuum blood tube with separation gel (usually yellow cap) to collect 6 ml of venous blood; avoid the occurrence of hemolysis and lipemia (If any, please specify).
4. Serum separation: 30 minutes after the collection of specimen, the specimen should centrifuge at the speed of 3000 rpm for 5 minutes within 2 hours. Divide supernatant into two collection tube without any additives, each tube should not less than 800μl. One tube sent to the central laboratory for detection, and storage the other tube as reserved sample. Attach the same number as registration form (Table 1), including name, gender, age, specimen collection time and collection unit.
5. Transportation and preservation of serum samples: serum frozen specimens should be placed in a low temperature refrigerator at -20 °C, the maximum of retention period is 6 months. Serum samples should be placed in a dry ice box while transportation. The refrigerator temperature should be recorded daily for future reference.

Table 1 Reserved sample record table and label manuscript

| Random No. | Patient name | Sex | Age | Blood collection date |
| --- | --- | --- | --- | --- |
|  |  |  |  |  |
| Hospital (detection of NT-proBNP in Qiliqiangxin study) | | | |  |

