# 2.3.1 . Inclusion criteria

1. Provision of signed informed consent prior to any study specific procedures;
2. Male or female, aged ≥18 years at the time of consent;
3. Established documented diagnosis of heart failure for at least three months ago according to “Chinese Heart Failure Diagnosis and Treatment Guideline” issued by the Chinese Medical Association Cardiovascular Branch.
4. Left ventricular ejection fraction (LVEF) ≤40% (echocardiogram, radionuclide, ventriculogram, contrast angiography or cardiac MRI );
5. NYHA cardiac functional grading II to III, with stable clinical symptoms; including those diagnosed as grade IV within 2 weeks before enrollment;
6. Serum NT-proBNP ≥ 450pg/ml;
7. Those who have received standardized baseline treatment regimens without doses adjusted and given intravenously for at least two weeks prior to enrollment;
8. standardized drug treatment includes: angiotensin-converting enzyme inhibitor (ACEI) or angiotensin receptor blocker (ARB) or angiotensin receptor neprilysin inhibitor (ARNI), beta blocker, and aldosterone receptor antagonist (the optimal therapeutic dose should be achieved, except for contraindications or intolerance);

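### Appendix 2 gives two incompatible collection procedures for the same NT-proBNP sample (3 ml EDTA plasma and 6 ml gel-tube serum), while the endpoint is worded as serum

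*Protocol*

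**What the plan says.** Protocol Appendix 2, under the heading NT-proBNP sample preparation process, starts with a short flow. It reads "Draw 3ml venous blood from each subject", then "EDTA anticoagulation", then centrifugation, with the supernatant kept and frozen at -20 °C.

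The numbered notes under the same heading describe a different collection:

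- Note 3: "Use a vacuum blood tube with separation gel (usually yellow cap) to collect 6 ml of venous blood".
- Note 4 turns to processing and names serum as the product. For the aliquots it says "Divide supernatant into two collection tube without any additives, each tube should not less than 800μl". One of the two tubes goes to the central laboratory and the other is held in reserve.
- Note 5 covers storage and transport, and speaks only of serum.

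Table 1, which closes this part of the appendix, names NT-proBNP and no other analyte.

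Elsewhere the protocol consistently says serum. Section 2.3.1, item 6, reads "Serum NT-proBNP ≥ 450pg/ml". The synopsis lists the rate of decrease in serum NT-proBNP as a secondary endpoint, section 4.1.2 lists its level, and section 9.2.3 plans a between-group comparison of serum values.

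**The concern.** Blood drawn into EDTA does not clot, so its supernatant is plasma. Blood in a plain separation-gel tube clots and yields serum. The appendix presents both as the way to prepare the one NT-proBNP sample. A site following the flow cannot comply with the notes, and the reverse also holds.

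Section 2.2 plans for over 100 centers, all working from this page. Some may follow the flow and others the notes, and a single site may change over time. If the assay reads the two specimens differently, part of the spread in the NT-proBNP endpoint would come from tube choice and not from patients or treatment. At stake are the precision and interpretability of one secondary endpoint.

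**Working it through.** The protocol states no figure on this point that could be reproduced. The check is a comparison of the text, one volume check and a little algebra.

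**1. The two instructions side by side (Appendix 2)**

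| | Flow | Notes 3 to 5 |
| --- | --- | --- |
| Draw | 3 ml | 6 ml |
| Tube | EDTA | separation gel |
| Specimen | plasma (follows from EDTA) | serum (stated) |
| Agrees with the serum wording of criterion 6 and the endpoint | no | yes |

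All three collection attributes differ. Both instructions are complete lines, so the clash is not a product of broken text.

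**2. Could both apply, to different things?** The heading covers only NT-proBNP, Table 1 names only NT-proBNP, and Note 4 sends a serum tube to the central laboratory. Nothing assigns one procedure to another analyte, site or visit.

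**3. Could they be one procedure, loosely written?** Inputs: Note 4 requires two aliquots of at least 800 μl; the draws are 3 ml and 6 ml.

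- Supernatant needed: 2 × 0.8 ml = 1.6 ml.
- Share of a 3 ml draw: 1.6 / 3 = 53%.
- Share of a 6 ml draw: 1.6 / 6 = 27%.

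Assume a haematocrit of 40 to 50% (not given in the protocol). The most that can be recovered is draw × (1 − haematocrit):

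- 3 ml: 3 × 0.50 = 1.5 ml to 3 × 0.60 = 1.8 ml.
- 6 ml: 6 × 0.50 = 3.0 ml to 6 × 0.60 = 3.6 ml.

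A 3 ml draw is borderline for the aliquot rule, and a 6 ml draw meets it comfortably. The aliquot rule therefore belongs with the 6 ml draw, and the flow reads as a separate procedure.

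**4. When would mixing disturb the endpoint?** Let B and F be a patient's baseline and follow-up values in one specimen type, and let the other type read k times as high.

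- Same type at both visits: (kB − kF) / (kB) = (B − F) / B. The factor cancels.
- Change of type between visits: 1 − kF / B = (1 − F / B) − (k − 1) F / B. The last term is spurious.
- Level instead of decrease: a patient measured in the other type reads kF instead of F, so even consistent sites would differ from each other by the factor k.

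The rate of decrease is thus disturbed only by a switch within a patient. The level is disturbed by any mixture of types. The protocol gives no value for k, so neither effect can be put into numbers.

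**The case against.** Much can be said for keeping this point small, and most of it stands.

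- **Mixing is possible, not shown.** The appendix permits it but does not prove that it will happen. Section 4 of Appendix 2 also refers to standard operating procedures for preparation, and a fuller laboratory instruction might settle the matter. However, the appendix itself carries the title of a standard operating procedure, and within the protocol nothing resolves the clash.
- **A proportional difference can cancel.** The algebra confirms this for a rate of decrease when each patient keeps one specimen type. It does not help the level named in section 4.1.2.
- **Time limits.** A reader might see a second contradiction between "All samples should be sent for test within 3 months after collection" and "the maximum of retention period is 6 months". The text does not support that. The first limits dispatch for testing and the second limits frozen storage. Note 4 creates a reserve tube that can stay in the freezer after its twin has gone, so the two limits are compatible.
- **Entry cut-off.** A reader might also infer that the 450 pg/ml threshold is being applied to two kinds of specimen. This is not established. Appendix 2 samples are labelled by drug number and logged by random number, identifiers that belong to randomization. They are collected in batches, by default when the center's work is done or, if enrollment is slow, within 2 months of the first patient. The laboratory then has 10 working days, and the monitor another week, to return results. That does not fit a decision between day -14 and day 0. Section 3.2.1 does send enrolment samples to the central laboratory, but the protocol does not say which assay decides eligibility. Criterion 6 matters here only because it, too, is worded as serum.

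**Conclusion.** The contradiction in tube, volume and specimen is real. The 3 ml EDTA flow also disagrees with the serum wording of the secondary endpoint and of criterion 6. The consequence is limited: specimen types may be mixed across centers or between a patient's visits, which would add variation unrelated to treatment to the NT-proBNP secondary endpoint.

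The size is unknown. It depends on the plasma-to-serum ratio and on how often sites would differ or switch, and the protocol gives neither. Any percentage, or any band of affected patients around the entry threshold, would be conjecture. The primary endpoint does not involve NT-proBNP and is not touched. Randomization balances the disturbance between arms in expectation, and blinding helps to keep it so. The loss is therefore one of precision and clarity, and no bias in favour of either arm is to be expected. This is a minor point, worth correcting because the correction is so cheap.

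**What to change.** In the flow of Appendix 2, replace the 3 ml and EDTA lines with the procedure of Notes 3 to 5, so that the page names one tube (separation gel), one volume (6 ml) and one specimen (serum). Add a sentence requiring that specimen type at every visit at which NT-proBNP is measured.

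Removing the gel-tube note instead would not do. It would leave EDTA plasma, and the serum wording in the synopsis and in sections 2.3.1, 4.1.2 and 9.2.3 would then have to change. The dispatch and retention limits can stay as they are.

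The cost is a change of appendix wording and a memo to sites. Sample size, visits and analysis are not affected.
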